## Assignment of interventions: allocation

### Sequence generation {16a}

The randomization sequence is based on http://www.randomization.com (Dallal GE) performed by an investigator not involved in patient clinical assessment before the start of enrollment to the study.

### Concealment mechanism {16}

The list is generated and accessed by one investigator, who provides the list to the hospital pharmacy department, where the capsules with drug or placebo are produced. The ward personnel, including the nurse administrating the capsules to the patients, and operating theatre personnel, including anesthesiologists, have no knowledge of patient group allocation.

### Implementation {16c}

All subjects who consent to participate and fulfill the inclusion criteria are randomly assigned to pregabalin or placebo groups. The principal investigator will receive the allocation sequence only after the last participant has completed the trial observation period.

## Assignment of interventions: blinding

### Who will be blinded {17a}

The participants, ward, operating theatre, and postoperative care unit personnel, as well as investigators assessing clinical data of the patients will be blinded to subject allocation.

## Data collection and management

### Plans for assessment and collection of outcomes {18a}

Data will be collected in 2 protocols: one for the intraoperative evaluation, filled in by the anesthesiologist, and one dedicated for the postoperative period, filled in by the PACU nurse. The nurses note data, such as oxycodone use from the PCA pump and pain scores (NRS) at specified time points, and record these in a dedicated protocol.

### Plans to promote participant retention and complete follow-up {18b}

Data will be collected during the hospital stay. At the end of the hospital stay, as a standard 24 h after the surgery, study subjects will be encouraged to fill in the QoR-40 questionnaire.

### Data management {19}

The data will be collected in paper form and stored in binders, to which only the principal investigator will have access. After data collection, investigators will check all forms for missing records. The data will be entered manually into an electronic database independently by one investigator, checked for accuracy by a second investigator, and stored on a secure database accessible with a personal login**.** After completion of the study, all data and study documents will be archived and stored by the principal investigator. The data is not public, but upon reasonable request, anonymous data can be made available.

### Confidentiality {27}

The data will be treated anonymously and confidentially, and the personal details of participants will not be revealed at any stage of the study. Every participant receives an ID number to anonymize data collection. The identifiable data will be stored separately in paper form in binders, whereas typed-in, anonymized, unidentifiable data will be stored only in electronic form in a secured database.

### Plans for collection, laboratory evaluation, and storage of biological specimens for genetic or molecular analysis in this trial/future use {33}

No biological specimens will be collected.

## Statistical methods

### Statistical methods for primary and secondary outcomes {20a}

We set the significance level at *α* = 0.05, consistent with common practice in the biomedical sciences, to minimize the probability of a Type I error, which involves incorrectly rejecting a true null hypothesis. The distribution of numerical variables was evaluated for normality using the Shapiro–Wilk test.

#### Statistical methods for numerical outcomes with one-time measurement

For numeric outcomes involving a single measurement point (e.g., total oxycodone consumption at 24 h, comparison of lowest and highest BP and HR values, duration of MBP below 65 mmHg or above 90 mmHg, HR below 50/min, and HR above 90/min, total fluid volume administered, total ephedrine usage during surgery, QoR-40 score at discharge), the significance of differences between the study group and the control group will be assessed using the Wilcoxon sum rank test. This non-parametric test is chosen based on the assumption that the distributions of these numerical variables do not conform to a normal distribution. For each outcome variable, the median and interquartile range (IQR) will be reported for both the study and control groups. In addition to the *p*-values, the Wilcoxon effect size (*r*) will be calculated to quantify the magnitude of the difference between the groups. Where possible, 95% confidence intervals for median differences between groups will be reported to provide an estimate of the precision of the observed effects.

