Concerning analgesic management in our study, remifentanil is a basic intraoperative opioid due to its rapid elimination and short time of action, which is in concordance with ERAS guidelines [1]. Moreover, it has been proven that these two drugs have a synergistic effect, which may be beneficial in the perioperative period but, on the other hand, may also cause an increased risk of adverse effects [13, 14]. Pregabalin also has an antihyperalgesic effect, possibly attenuating opioid-induced hyperalgesia sparked by remifentanil [6].

In addition, as pregabalin is a promising element of multimodal analgesia strategy, we plan to measure intraoperative parameters relating to patient hemodynamical stability such as heart rate (HR), systolic blood pressure (SBP), diastolic blood pressure (DBP), and mean blood pressure (MBP) every 5 min as well as cumulative doses of vasopressors needed, atropine used to treat bradycardia and administered fluid volume. In our study, we hypothesized that pregabalin might have little or no effect on hemodynamical stability in contrast with most commonly used co-analgesics such as lidocaine, dexmedetomidine, or magnesium sulfate [1, 15–18]. Its possibly negligent impact on the circulatory system would be beneficial as obese patients undergoing LSG are particularly prone to hemodynamic disturbances [19, 20], and hypotension may in these patients spark complications like myocardial infarction or kidney failure [21].

To our knowledge, there are no known studies assessing the impact of pregabalin on patient recovery after LSG, with a specific focus on its sedative effects, in isolation from other medications such as dexmedetomidine [10, 11]. As we hypothesized that pregabalin may have a beneficial impact in this field, such an effect will be measured in the postoperative period on both an objective scale and by filling out the Quality of Recovery-40 questionnaire (QoR-40), constructed to measure patient’s experience after a broad spectrum of surgeries [22].

In conclusion, considering the limited number and inconsistent results of available studies on the effect of preemptive pregabalin administration in obese patients on opioid consumption, pain scores, the incidence of opioid side effects, and hemodynamical stability, we decided to conduct our randomized, prospective, double-blind study.

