### Objectives {7}

Our study aims to assess, in the patients with obesity undergoing LSG, what is the difference in total oxycodone consumption (applied by the PCA pump) between preemptive oral pregabalin 150 mg administration compared with placebo, 24 h after the operation. We hypothesized that the investigated intervention would reduce opioid use and improve recovery with potentially fewer opioid side effects, as well as provide similar intraoperative hemodynamical stability.

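### For ephedrine dose and time outside blood pressure or heart rate limits, the only planned measure of precision, a CI for the median difference, can shrink to 0 to 0 if most patients score zero

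*Protocol article*

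**What the plan says.** The section on numerical outcomes with one-time measurement treats a mixed list in one way. Oxycodone, extreme blood pressure and heart rate values, fluids and QoR-40 stand beside "duration of MBP below 65 mmHg or above 90 mmHg, HR below 50/min, and HR above 90/min" and "total ephedrine usage during surgery". For all of them the group difference "will be assessed using the Wilcoxon sum rank test". Each arm gets a median and IQR, and the effect size r is added. Then, with the qualifier that this applies where possible: "95% confidence intervals for median differences between groups will be reported to provide an estimate of the precision of the observed effects". The section names neither the estimator nor the interval method, and it has no separate rule for outcomes with many zeros.

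The Objectives section hypothesises that pregabalin will reduce opioid use and improve recovery, "as well as provide similar intraoperative hemodynamical stability", and gives no margin. The Background section lists "cumulative doses of vasopressors needed" among the measures of stability. The section on the statistical tool and packages says that the statistical analysis plan is integrated in this protocol, so the one-time-measurement section is where the rule belongs.

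**The concern.** Ephedrine dose is zero in a patient who is given none, and time beyond a limit is zero in a patient who never crosses it. If such patients are the majority in both arms, both medians are 0, and so is their difference. The interval around that difference can also be 0 to 0, whatever happens among the patients above zero.

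This matters because similar stability is a hypothesis of the trial. A claim of similarity rests on the width of an interval: it must exclude differences that would matter. A zero-width interval looks like perfect precision and contains no information about that. No interval is planned for r, and the IQR describes spread among patients, not uncertainty about the group difference. Nothing else in the plan fills the gap for these outcomes.

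**Working it through.** **Inputs from the document.** 90 patients allocated 1:1, so 45 per arm (Sample size; Trial design). Two-sided alpha is 0.05. The plan has no figure of its own to reproduce here, because it gives no share of patients with zero ephedrine or zero time outside a limit. All such shares below are assumptions.

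**Why a rank-based interval collapses.** The usual interval for a shift takes order statistics of all pairwise differences. With 45 per arm there are 45 × 45 = 2025. The lower rank is

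2025/2 − 1.96 × √(2025 × 91/12) = 1012.5 − 242.9 = 769.6, rounded down to 769.

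The interval is exactly 0 to 0 when at most 768 differences are positive and at most 768 are negative, that is, at most 768/2025 = 37.9% each.

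If a share a of one arm and b of the other are above zero, the expected share of positive differences is about a(1 − b) + ab/2 (ties among users ignored, similar doses in users):

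- 20% v 10%: 0.18 + 0.01 = 0.19
- 30% v 15%: 0.255 + 0.0225 = 0.28
- 40% v 20%: 0.32 + 0.04 = 0.36
- 60% v 40%: 0.36 + 0.12 = 0.48

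The first two lie well below 0.379, the third just below it, and the fourth above it. Collapse should therefore be near certain, common, and then rare.

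**Simulation, 45 per arm, use twice as frequent in one arm** (assumed doses of 5 to 30 mg in users):

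| Use | Rank-based CI is 0 to 0 | Bootstrap CI of median difference is 0 to 0 | Wilcoxon p < 0.05 |
|---|---|---|---|
| 20% v 10% | 100% | 99% | 26% |
| 30% v 15% | 95% | 79% | 40% |
| 40% v 20% | 66% | 28% | 54% |

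The 0-to-0 interval stood beside a non-significant p-value in about 73%, 59% and 46% of trials.

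**How it depends on the share of zeros** (same share in both arms, 45 per arm; non-zero values an assumed lognormal rounded to steps of 5):

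| Zeros | Rank-based CI is 0 to 0 | Bootstrap CI is 0 to 0 |
|---|---|---|
| 20% | 0% | 0% |
| 40% | 4% | 0% |
| 50% | 35% | 0% |
| 60% | 78% | 10% |
| 70% | 97% | 64% |
| 80% | 100% | 99% |

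With 38 per arm (the 76 evaluable patients), the rank-based figures at 60% and 70% zeros are 68% and 94%. When use is 60% v 40% or more, collapse occurs in 8% of trials or fewer.

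**What a risk difference would show instead.** Take observed use of 30% v 15% with 45 per arm. The standard error is √(0.30 × 0.70/45 + 0.15 × 0.85/45) = √0.0075 = 0.0866. The risk difference is 0.15, with a 95% CI of 0.15 ± 1.96 × 0.0866, or −0.02 to 0.32. That interval says openly that the data do not establish similarity. The median difference from the same trial would most often read 0 (0 to 0).

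**The case against.** Four points against the concern have weight.

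- **The interval is conditional.** The text promises it only where possible, and a degenerate case could be thought excluded. But a 0-to-0 interval can be computed, so the phrase does not clearly exclude it, and nothing is named to take its place.
- **Other statistics stand beside it.** The p-value and r come from the rank-sum test and do not vanish when both medians are 0. The IQR helps too: at 30% v 15% and 40% v 20% use, the expected upper quartile is above zero in one arm and zero in the other. This is right, and it limits the harm. It does not supply precision: r has no planned interval and is not in mg or minutes, and in about half to three quarters of the simulated trials the p-value was non-significant beside the 0-to-0 interval.
- **The share of zeros is unknown.** The Background section describes these patients as especially prone to haemodynamic disturbance, which points, if anything, to fewer zeros. This stands, and the point is therefore conditional. The remark is qualitative, though, and cannot show that most patients will be above zero on each outcome.
- **Size depends on the interval method.** It does: at 60% zeros in both arms, 78% for the rank-based interval against 10% for the bootstrap. Both collapse as zeros become more frequent.

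A reader might go further and infer that the plan will falsely show equal stability. The document does not support that. It has no rule or margin by which similarity would be concluded from this interval, and stability is also judged on the highest and lowest pressures and heart rates and on fluid volume, which would not pile up at zero.

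**Conclusion.** The concern holds in conditional form. For total ephedrine and the time-outside-limit outcomes, the one planned measure of precision can become uninformative. If about 60% or more of patients are at zero, both medians are usually 0. With use of 40% v 20% down to 20% v 10%, the interval is 0 to 0 in about 66% to 100% of simulated trials (rank-based) or 28% to 99% (bootstrap). It can then appear to support similar stability although use differs twofold. Around half zeros the problem is smaller and depends on the method. At 40% zeros or fewer it is rare.

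The figures rest on assumed shares of zeros, assumed dose distributions and an interval method that the plan leaves open. The document does not support the stronger claim that most patients will be at zero. The Wilcoxon test remains valid, and the point concerns secondary outcomes only. It is a worthwhile and cheap improvement.

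**What to change.** For total ephedrine and for time with MBP <65 or >90 mmHg and HR <50 or >90/min, keep the Wilcoxon p-value and r. In place of the median-difference interval, report:

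1. the number and percentage in each arm with any use, or any time outside the limit, with a risk difference and 95% CI;
2. the difference in means (mg or minutes) with a bootstrap 95% CI. This also serves where nearly everyone crosses a limit and the proportion says little.

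Add that statements about similar stability on these outcomes will rest on those intervals. The median-difference interval can stay for the other one-time outcomes.

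The cost is a sentence or two in the analysis section and a few more table rows. No new data are needed, the tests and their power do not change, and the primary analysis is untouched.

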#### Statistical methods for numerical outcomes with multiple measurements

Estimation of the differences between the treatment and control groups for the numerical variables, specifically the NRS score and the PONV-Impact score was conducted using a Repeated Measures Linear Mixed Effects Regression (RLMER) model. This approach was chosen to appropriately handle the intrinsic correlation within patient-level repeated measures data collected at multiple time points. The RLMER model was structured to include fixed effects for the treatment group, time points, and the interaction between the treatment group and time, allowing us to assess how treatment effects vary over time. Additionally, patient-specific random intercepts were incorporated to account for individual variability in baseline scores, which assumes that each patient has a unique starting point that affects all their measurements. We also controlled for potential confounders (e.g. sex, age, BMI) by including them as fixed effects in the model (see Additional file 1: Appendix A for the RLMER model specification).

The effect sizes (Cohen’s *d*) between the treatment and control groups at each specific time point were estimated through contrast analysis, utilizing the estimation of marginal means (EMMs).

#### Statistical methods for dichotomic outcomes with multiple measurements

For the dichotomous outcomes, specifically for instances of SatO2 falling below 94% and the occurrence of blurred vision, differences between the treatment and control groups at each time point were systematically analyzed using a Generalized Linear Mixed Effects Model (GLMER) with a logit link function. This model was chosen to appropriately handle the binary nature of the data, where the outcomes were coded as 1 for events (i.e., SatO2 below 94% or blurred vision) and 0 otherwise. The differences between groups at each time point were quantified using Odds Ratios (ORs), derived from the estimated marginal means (EMMs) of the fitted GLMER model. Odds Ratios represent the odds of the event occurring in the treatment group relative to the control group, adjusted for other model factors. The ORs, along with their 95% confidence intervals and *p*-values, were presented at each time point to assess the strength and significance of the group differences. These results provide insights into how the likelihood of adverse outcomes (low SatO2 or blurred vision) varies between the treatment and control groups across different time points.

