### Outcomes {12}

The primary outcome measure will be total oxycodone consumption 24 h after surgery. Secondary outcome measures will be as follows: pain scores on the NRS scale at 1, 6, 12, and 24 h after surgery, postoperative sedation on the Ramsay scale [25], PONV impact scale [26], the incidence of desaturation episodes < 94% and episodes of blurred vision at 1, 6, 12 and 24 h after surgery, intraoperative heart rate (HR), systolic blood pressure (SBP), diastolic blood pressure (DBP), mean blood pressure (MBP): their highest and lowest values, time of MAP < 65 mmHg, > 90 mmHg, HR < 50 and > 90, total fluid volume, total ephedrine dose and patient's comfort assessed in QoR-40 [22] questionnaire at discharge.

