### Sample size {14}

The primary outcome of the study is 24-h oxycodone consumption. The mean 24-h oxycodone consumption in our previous study was 31.31 mg in patients on multimodal anesthesia [18] and SD was 13.7. In order to calculate sample size, we made the following assumptions: type 1 error (*α*) was set at 0.05; type 2 error (*β*) at 0.9 based on two-tailed testing. We considered a difference between groups (*δ*) greater than 10 mg, this being roughly 30% of the mean dose given above, and a standard maximal single dose of oxycodone in an adult patient, to be clinically significant. Using a sample size formula for two-tailed testing recommended in [27], a sample size of 76 should be enough to detect a substantial difference, as stated above. Taking into account an assumed mean drop-out of 15%, we have adopted a rounded-up sample size of 90 patients.

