### Adverse event reporting and harms {22}

Most reported adverse effects caused by pregabalin were mild to moderate intensity, dose-dependent, and occurred within the first 2 weeks of initiating treatment. The most common adverse reactions reported across all patient populations in premarketing controlled trials, which occurred in greater than or equal to 5% of patients taking pregabalin and twice the rate reported by patients receiving placebo, were: somnolence, dizziness, blurred vision, difficulty with concentration/attention, dry mouth, edema, and weight gain [40].

In our trial, participants will be advised to contact ward personnel as soon as possible in case of unexpected or adverse effects or any discomfort supposedly associated with the capsule intake. All the patients will be supervised during their hospital stay, and all possible adverse events or reactions will be observed, recorded, and reported in the study.

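### The plan names no method for time points at which an arm has no events, a likely pattern for blurred vision if event rates are low and a conditional one for desaturation

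*Protocol article*

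**What the plan says.** The section on dichotomic outcomes with multiple measurements covers two outcomes, "specifically for instances of SatO2 falling below 94% and the occurrence of blurred vision", each coded 0 or 1. The model is a "Generalized Linear Mixed Effects Model (GLMER) with a logit link function". On the contrast it says: "The differences between groups at each time point were quantified using Odds Ratios (ORs), derived from the estimated marginal means". The reporting rule is explicit: "The ORs, along with their 95% confidence intervals and *p*-values, were presented at each time point". Outcomes {12} fixes the times, for example "episodes of blurred vision at 1, 6, 12 and 24 h after surgery", and Table 1 gives the same four.

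The model section states no expected event rate and no alternative if events are sparse. The only rate information for either outcome is under Adverse event reporting and harms {22}. It lists blurred vision among reactions that occurred, in premarketing trials, in "greater than or equal to 5% of patients taking pregabalin and twice the rate reported by patients receiving placebo". Sample size {14} says that "a sample size of 76 should be enough to detect a substantial difference" and continues: "Taking into account an assumed mean drop-out of 15%, we have adopted a rounded-up sample size of 90 patients". The section on the statistical tool says that the analysis plan is integrated in the article and that no separate detailed plan will be published.

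**The concern.** A separate OR for each time point implies a group-by-time term in the model. With that term, a group-by-time cell without events pushes the log-OR for that time point to plus or minus infinity under maximum likelihood. If both arms are empty, the OR is undefined. The Wald standard error, interval and p-value then carry no information. A patient random intercept does not prevent this, because the fixed effect for the empty cell can still diverge.

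The trial is sized for oxycodone consumption, with about 40 patients per arm, so a low event rate at one time point can easily leave an arm empty. The analysts would then have to print an unusable OR or choose a replacement after seeing the data. Blurred vision is a prespecified secondary outcome and a listed reaction to the study drug, so this choice should not be left until then.

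**Working it through.** **Patients per arm.** The stated total of 76 gives 76/2 = 38 per arm at 1:1. The dropout step reproduces: 76/0.85 = 89.4, rounded up to 90, or 45 per arm. The 76 itself does not quite reproduce. With a difference of 10 mg, SD 13.7, two-sided alpha 0.05 and 90% power, the z formula gives 2 × (1.960 + 1.282)² × 13.7²/10² = 39.4, so 40 per arm and 80 in total. This is a side remark, since 40 lies between the two values used below: 38 (after the assumed dropout) and 45 (no dropout).

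**Event rates (assumed).** The article gives no rate per time point. For blurred vision the lower bound of its class is 5% on pregabalin and, at half that, 2.5% on placebo. I assume that this applies at each time point, then vary it upwards.

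**Empty arm at one time point.** With n per arm and event rates pT and pC:

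- P(no events in an arm) = (1 − p)^n
- P(at least one arm empty) = 1 − [1 − (1 − pT)^n] × [1 − (1 − pC)^n]

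At 5% vs 2.5%:

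- n = 38: 0.95^38 = 0.142 and 0.975^38 = 0.382, so 1 − 0.858 × 0.618 = 0.47. Expected number of affected ORs: 4 × 0.47 = 1.9.
- n = 45: 0.95^45 = 0.099 and 0.975^45 = 0.320, so 1 − 0.901 × 0.680 = 0.39. Expected number: 4 × 0.39 = 1.6.

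**At least one of the four ORs affected.** If time points are independent, this is 1 − (1 − q)^4, where q is the probability for one time point. For q = 0.47 it is 1 − 0.53^4 = 0.92. Correlation within patients lowers it. A simulation of 4,000 trials per setting, with a patient random intercept of SD 0, 2 or 3 on the logit scale and the marginal rates held fixed, gives the lower ends below. The upper ends correspond to independence.

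| Assumed rate per time point, pregabalin vs placebo | One time point, 38 per arm | One time point, 45 per arm | Any of four, 38 per arm | Any of four, 45 per arm |
|---|---|---|---|---|
| 5% vs 2.5% | 0.47 | 0.39 | 0.82–0.92 | 0.76–0.86 |
| 10% vs 5% | 0.16 | 0.11 | 0.40–0.50 | 0.30–0.37 |
| 20% vs 10% | 0.018 | 0.009 | 0.06–0.07 | 0.03–0.04 |

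Below the floor it gets worse: at 2% vs 1% the probability for one time point is 0.83 (38 per arm) or 0.78 (45 per arm).

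**Desaturation.** With no rate to start from, the useful question is where the problem stops. For equal rates p in both arms and n = 38, set 1 − [1 − (1 − p)^38]² = 0.10. Then (1 − p)^38 = 1 − √0.90 = 0.0513, so p is about 7.5%. Above that rate the chance of an empty arm at a given time point is below 10%; above about 9.2% it is below 5%. At 20% in both arms it is 0.0004.

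**The case against.** The strongest counter-argument is that the size rests on a rate the trial has not stated. The 5% is a floor for a class of reactions in premarketing trials, not a rate per time point after one preoperative capsule, and the probability falls quickly as the rate rises. Planned enrolment is 45 per arm and the article expects little missing data, so 38 is the less favourable case. Both points stand, which is why the results are shown as ranges. At 10% vs 5% and 45 per arm, about one trial in three would still lose at least one OR.

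Second, the binary model is not printed as an equation. The group-by-time term is inferred from the promise of an OR at each time point; without it, one empty cell would not make an OR inestimable. Neighbouring sections place model specifications in additional files that are not shown, so a fallback could be written there. This limits the point to the text shown. It cannot simply be deferred to a later plan, because the article says that it contains the analysis plan.

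A reader might go further in three ways that the documents do not support:

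- That desaturation ORs will often be lost too. No desaturation rate is given, and the background describes these patients as prone to respiratory complications, which points towards more frequent events.
- That the analysis would give no usable result. Even at the floor with 38 per arm, about 1.9 of four ORs are affected on average and the others have events in both arms. Adverse events are also to be recorded and reported in any case.
- That the model would usually fail to converge. The check counted empty cells and fitted no models, so it says nothing on how often the software would fail.

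**Conclusion.** The point holds in a limited form. The article commits to a maximum-likelihood logit mixed model with an OR, CI and p-value at each of four time points, and the text shown has no route for an arm without events. For blurred vision near the article's floor rate, losing at least one of the four ORs is the expected outcome. At about twice the floor it happens in roughly a third to a half of trials; at four times the floor it is a minor risk. For desaturation the plan is exposed only if the rate per arm and time point is below roughly 7–10%.

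The conclusion rests on three assumptions: the rates per time point, a group-by-time term in the model, and 38 to 45 evaluable patients per arm. These are secondary outcomes, and the oxycodone analysis is untouched. Because the remedy is cheap and must be chosen before the data are seen to be credible, the change should be made.

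**What to change.** Keep the contrasts at 1, 6, 12 and 24 h, since seeing how group differences change over time is the stated aim. Then:

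- Name a penalised logit model (Firth-type or with a stated weak prior) as the estimation method for both binary outcomes, and state the group-by-time term explicitly.
- Report event counts and denominators by arm at each time point beside the ORs.
- Add, as a supplement and not a replacement, a per-patient summary of any event within 24 h: risk difference with a Newcombe or exact 95% CI, and an exact test.

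The cost is a few lines of analysis text, a little more programming and ORs that are slightly shrunken towards 1. No new data or patients are needed. If an additional file already names a method for sparse cells, a cross-reference in the main text would do instead.
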